### Inclusion criteria

All volunteers will have a diagnosis of myogenous TMD based on the RDC/TMD, with moderate to severe pain in the masseter and temporal muscles being rated by an expert dentist. To standardize the sample, the body mass index of all participants must be less than 25 kg/m2, as the amount of adipose tissue between the electrode and surface of the muscle can affect that reading of the electromyographic (EMG) signal [15]. All volunteers must also have an initial pain score greater than 3 points on the VAS [16].

### Exclusion criteria

The exclusion criteria will be missing teeth, the use of dentures, systemic or neuromuscular diseases, a history of trauma to the face or temporomandibular joint, history of temporomandibular joint luxation, currently undergoing orthodontic treatment, or currently undergoing medicinal treatment that can affect the musculoskeletal system (analgesic, anti-inflammatory agent or muscle relaxant).

### Procedures

The proposed study will follow the recommendations of the Consolidated Standards of Reporting Trials (CONSORT) statement to ensure greater transparency and quality of the findings. The participants will receive information on the objectives and the eligibility criteria of the study, and will subsequently provide informed consent. For eligible participants, the evaluator will collect the baseline data prior to randomization. This evaluator will be blinded to the allocation of the patients to the different groups. The following assessment tools will be applied: 1) RDC/TMD questionnaire for the diagnosis and inclusion of the participants; 2) EMG; 3) VAS for pain; and 4) an algometer. Detailed descriptions of each of these tools are offered below.

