#### Initial evaluation

The individuals who meet the eligibility criteria will undergo an initial evaluation in the following sequence: VAS, algometry for pain and EMG analysis on the masseter and anterior temporal muscles.

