Phototherapy will be applied by one of the researchers in an isolated room with only the researcher and the volunteer present. The researcher will receive the pre-programmed hand piece. Both the researcher and volunteer will be wearing eye protection equipment. The volunteer will be in the supine position on a cot with lower limbs supported on a roll of foam rubber measuring 20 cm in diameter and head supported on a pillow to provide a comfortable resting posture. Phototherapy will be applied using the point technique in contact with the skin with a beam area of 4 cm^2^ (device aperture). The placebo group will be submitted to the same procedures as the groups submitted to phototherapy. Only the coordinator will have knowledge regarding the different phototherapy and placebo applications. At the end of the study, the individuals in the placebo group will be submitted to treatment with active phototherapy.

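### The only pre-treatment VAS described is both the entry gate (above 3) and the outcome baseline, so within-arm pain falls are overstated by regression to the mean

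*Protocol article*

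**What the plan says.** All references are to the protocol article.

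- **Abstract, Methods/Design:** the assessments take place on four occasions: baseline, immediately after, 24 h after and 48 h after phototherapy. Only one precedes treatment.
- **Inclusion criteria:** "All volunteers must also have an initial pain score greater than 3 points on the VAS". A separate criterion asks for a myogenous TMD diagnosis, "with moderate to severe pain in the masseter and temporal muscles being rated by an expert dentist".
- **Initial evaluation:** "The individuals who meet the eligibility criteria will undergo an initial evaluation in the following sequence: VAS, algometry for pain and EMG analysis". The VAS is its first item.
- **Procedures:** "The participants will receive information on the objectives and the eligibility criteria of the study, and will subsequently provide informed consent". Then: "For eligible participants, the evaluator will collect the baseline data prior to randomization". The only tool listed with an inclusion role is the "RDC/TMD questionnaire for the diagnosis and inclusion of the participants"; the VAS is listed without one.
- **Visual analog scale:** the participant marks current pain on a 10 cm line.
- **Data analysis:** pain by VAS and algometer is the primary outcome. Intra-group comparisons over time are planned (repeated-measures ANOVA or Friedman, then paired tests) alongside inter-group comparisons (one-way ANOVA or Kruskal-Wallis). Cohen's d is to express clinical effect size.
- **Background:** the hypothesis includes persistence of the single-session effect to 24 and 48 hours.

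**The concern.** The sections do not fit together. Inclusion criteria needs an *initial* VAS to decide who is eligible. Initial evaluation, which contains the VAS, takes only people already eligible. No other VAS before treatment is described. Either one mark does both jobs, or there is an earlier screening mark that the article does not mention.

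The difference matters. A single VAS mark is a person's usual pain plus short-term fluctuation. Requiring that mark to exceed 3 admits people partly because they were having a bad moment. When the same mark is the baseline, later marks drift back toward the usual level in all four arms, placebo included. A test of change within an arm cannot tell that drift from relief due to phototherapy. No volunteer needs to misreport for this to happen.

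**Working it through.** **1. Is there one VAS or two before treatment?** Four assessment occasions minus three after treatment leaves one. The RDC/TMD is the only tool given an inclusion role. The entry score and the evaluation share the word *initial*. The only pre-treatment VAS described is therefore the one that must also supply the entry score.

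**2. Inputs.** From the document: cut-off 3, 18 per arm, 5% significance level. Assumed, because the document gives no VAS distribution: VAS among those screened is normal, SD σ = 2 cm, mean μ = 3.5 to 5.5 cm; correlation r between two untreated marks on the same person = 0.5 to 0.85. The protocol states no figure for this drift, so there is none to reproduce.

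**3. Built-in fall with no treatment effect.** With z = (3 − μ)/σ and λ = φ(z)/(1 − Φ(z)), the expected fall is (1 − r) × σ × λ.

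| μ | z | λ | r | Fall (cm) |
|---|---|---|---|---|
| 3.5 | −0.25 | 0.3867/0.5987 = 0.646 | 0.5 | 0.5 × 2 × 0.646 = 0.65 |
| 4.5 | −0.75 | 0.3011/0.7734 = 0.389 | 0.7 | 0.3 × 2 × 0.389 = 0.23 |
| 5.5 | −1.25 | 0.1826/0.8944 = 0.204 | 0.85 | 0.15 × 2 × 0.204 = 0.06 |

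**4. Effect on a within-arm paired t-test, n = 18, two-sided 5%.** Variance of the gated baseline: V = σ²(1 + zλ − λ²). Variance of the change: (1 − r)²V + σ²(1 − r²). Noncentrality is fall × √18 / SD of change; the false-positive rate is read from the noncentral t with 17 df, treating the changes as normal.

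| μ, r | V | SD of change | Noncentrality | False positives |
|---|---|---|---|---|
| 3.5, 0.5 | 1.69 | √(0.25 × 1.69 + 3.00) = 1.85 | 1.48 | about 29% |
| 4.5, 0.7 | 2.23 | √(0.09 × 2.23 + 2.04) = 1.50 | 0.66 | about 10% |
| 5.5, 0.85 | 2.81 | √(0.0225 × 2.81 + 1.11) = 1.08 | 0.24 | about 6% |

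An intermediate case, μ = 4 and r = 0.5, gives about 19%. With a separate, ungated VAS as baseline the expected fall is 0.00 cm and the rate returns to about 5%.

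**5. Pre-post Cohen's d from drift alone**, taken as fall/√V: 0.65/1.30 = 0.50, 0.23/1.49 = 0.16 and 0.06/1.68 = 0.04. The protocol's own labels are small at 0.2 and moderate at 0.5, so in the least favourable case drift alone comes close to the moderate label.

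**6. Between arms.** The gate acts before randomization, so the expected drift is the same in each arm and cancels in any difference between arms. A simulation with 18 per arm, μ = 4, r = 0.7 and no treatment effect gave 5.1% false positives for the four-arm comparison and a difference of about 0.00 cm between the 7.86 J and placebo arms. That simulation also let half of those scoring 1 to 3 mark above the cut-off.

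**The case against.** The strongest reply is that eligibility is settled before baseline. Initial evaluation and Procedures both speak of people who are already eligible, and the research-design overview puts selection after screening. Read literally, that is nearly the order recommended here. If an undescribed screening VAS exists and baseline is taken afresh, the drift disappears. This stands as a limit: that one mark does both jobs is the best reading of what is described, but the document never says so outright. It does not remove the need to reconcile the sections, because the text supplies no second VAS.

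A second reply is that the randomized, blinded comparison with placebo is sound. That stands in full.

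A third is that the dentist's rating also restricts entry. It may raise mean pain before the VAS gate applies, which moves the result toward the lower end of the range. It does not remove the gate.

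A reader might go further and infer that volunteers learn the passing mark and score themselves above it, since "At the end of the study, the individuals in the placebo group will be submitted to treatment with active phototherapy". The document does not support this. Procedures says that eligibility criteria are explained before consent, which is ordinary practice; it does not say that the number 3 is disclosed. Nor does any section say that volunteers know of the later active treatment when they mark the scale. A reader might also infer that admitting people with little pain shrinks the differences between doses. Nothing in the document shows this or allows it to be sized.

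**Conclusion.** The concern holds in a limited form. As described, the qualifying VAS is also the baseline of a primary outcome, and that overstates within-arm pain reduction in all four arms. Under the assumed values the fall is 0.06 to 0.65 cm on a 10 cm scale, and a within-arm paired test at 18 per arm would be falsely significant about 6% to 29% of the time against a nominal 5%. The range depends wholly on the assumed SD, mean and repeatability, and on there being no unreported screening VAS.

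The intra-group tests, any pre-post Cohen's d and any within-arm claim that the effect lasts to 24 and 48 hours are exposed. The comparisons between doses and with placebo are not. This is a minor point, worth correcting because the correction is cheap.

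**What to change.** 1. Take the qualifying VAS at the RDC/TMD screening examination and record it as a screening value only.
2. Take a separate VAS at the initial evaluation, use it as the only outcome baseline, and do not apply the cut-off to it again.
3. Reword Inclusion criteria, Initial evaluation and Procedures so that all three give this order and name the two marks differently.

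The cost is one extra VAS mark per volunteer and some wording. The downside is that some participants will have a baseline VAS at or below 3. The Trial status section says recruitment is under way, so the change can help only those not yet enrolled. For those already enrolled, the report should state whether their baseline was the qualifying mark, and claims of effect and of its persistence should rest on the between-arm comparisons.

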### Diagnosis of temporomandibular disorder

The RDC/TMD will be used for the diagnosis of TMD [17], which classifies individuals into three main groups: I) muscle disorder; II) disc displacement; and III) other joint conditions (Table 1). Each participant may be classified in one, two or three groups simultaneously. As pain will be the primary outcome of the study, all volunteers will need to have myofacial pain. Therefore, the RDC/TMD will be used to determine whether the volunteers meet this inclusion criterion. The RDC/TMD has two axes. Axis I consists of a clinical exam, which will be performed by a single examiner having previously undergone a training and calibration exercise in compliance with the specifications of the International RDC/TMD Consortium. This exam addresses the presence of spontaneous muscle and joint pain, maximum mouth opening, mandibular range of motion, joint sounds and pain sensitivity during mandibular movements or upon palpation of the muscles and/or joint. Average duration for the application of Axis I is 20 minutes. The volunteer will be seated in a chair with the trunk erect, back completely supported, feet on the floor and hands supported on the thighs, with the Frankfurt plane parallel to the ground. The examiner will be positioned in front of the volunteer. Axis II classifies individuals based on the degree of chronic pain, depression and nonspecific physical symptoms. This axis will be self-administered following the clinical exam in a well-lit, climate-controlled room with no time constraints.

**Table 1 Tab1:** **Classification and diagnosis of temporomandibular disorder subgroups based on Research Diagnostic Criteria for Temporomandibular Disorders**

Group	Subgroup
I	A. Myofascial pain
	B. Myofascial pain with limited opening
	No group I diagnosis
II right	A. Disk displacement with reduction
	B. Disk displacement without reduction with limited opening
	C. Disk displacement without reduction without limited opening
	No group II diagnosis
II left	A. Disk displacement with reduction
	B. Disk displacement without reduction with limited opening
	C. Disk displacement without reduction without limited opening
	No group II diagnosis
II right	A. Arthralgia
	B. Osteoarthritis of temporomandibular joint syndrome (TMJ)
	C. Osteoarthritis of TMJ
	No group III diagnosis
II left	A. Arthralgia
	B. Osteoarthritis of TMJ
	C. Osteoarthritis of TMJ
	No group III diagnosis

### Electromyography

Electromyography (EMG) activity of the right and left masseter and anterior temporal muscles will be recorded using disposable, active surface electrodes (Ag/AgCl - Noraxon™- http://www.noraxon.com/*webcite* - [name]. [contact]) attached to the belly of the muscles in the region of greatest volume determined during moderate jaw clenching. The skin surface will be cleaned with cotton soaked in 70% alcohol to diminish impedance [15]. A metallic rectangular reference electrode measuring 3 × 2 cm coated with Lectron II conductive gel (Pharmaceutical Innovations™ http://www.pharminnovations.com*webcite* - [name] [name]) to enhance the conduction capacity and impede interference from external noise will be attached to the left wrist of each participant.

The EMG signals will be collected with the aid of an eight-channel electromyograph (830 C module, EMG System do Brazil Ltda™)- http://www.emgsystem.com.br*webcite* - [name]. [contact][name])) using a band-pass filter with a cutoff frequency of 20 to 1000 Hz and common-mode rejection ratio >120. All data will be collected and processed using 16-bit analog-digital converter (EMG System do Brazil Ltda™ - http://www.emgsystem.com.br*webcite* - [name]. [contact][name]))) with a sampling frequency of 2 kHz. The signal capturing module will be connected to a standard laptop computer with a compatible data acquisition program.

The volunteer will be seated in a chair, with the back completely supported, eyes open, feet parallel on the a rubber mat and arms supported on the thighs. The exam will be carried out under three conditions: 1) in the normal postural position with the mandible at rest; 2) during maximum voluntary contraction (MVC) with Parafilm M™ placed between the teeth; and 3) during maximum habitual contraction (MHC) with no material placed between the teeth. In the normal postural position, the volunteer will remain with the mandible relaxed, teeth apart and lips in contact for 15 s. For the MVC, the volunteer will be instructed to position Parafilm M™ between the upper and lower premolars, first molars and second molars bilaterally and perform isometric contraction for 5 s following a verbal command. For the MHC, the same procedure will be performed without the use of M™ for 5 s. Under each condition, three readings will be made with a 2-minute rest interval between readings to avoid fatigue.

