### Electromyography signal processing

The root mean square (RMS), median frequency, asymmetry index and co-contraction index will be used as the parameters for the interpretation of the signal processing. The signals will be processed using specific routines developed with the aid of the Matlab program, version 7.1 (The MathWorks Inc., Massachusetts, USA). The RMS of the signal (expressed in μV) obtained at rest and during MHC will be normalized by the largest RMS obtained during three readings of MVC (μmV/μV × 100: %MVC). With the mandible at rest, the RMS will be calculated for the entire 15 s of the signal collected. Data on MHC will be analyzed based on Ferrario *et al*. [18], with the first and last second of the raw EMG signal being discarded and the RMS being calculated using a 25-ms moving window without overlap for the 3 s of signal selected.

The overlap percentage coefficient (OPC, unit: %) described by Ferrario *et al*. [18] will be used to evaluate the distribution of muscle activity in time and the amplitude determined by the occlusion. Symmetric distribution of muscle activity determined by the OPC will be analyzed considering variability between 0% (absence of symmetry) and 100% (perfect symmetry). Lateral excursion (potential given by imbalanced contractile activities of the contralateral masseter and temporal muscles) will be evaluated using the torque coefficient (TC, unit: %) considering variability between 0% (absence of lateral excursion force) and 100% (maximum lateral excursion force).

The EMG signal of the paired muscles under each situation recorded during MHC will be compared by calculating a percentage of OPC and TC. Mean normalized EMG activity (%MVC) of the right and left masseter and temporal muscles will be calculated and used for comparisons among evaluation times (pre-treatment, immediate post-treatment and late post-treatment).

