### Data analysis

Pain will be the primary outcome and will be determined using a VAS and algometer. EMG will be the secondary outcome. The independent variables will be the different light sources used for phototherapy. The dependent variables will be derived from the pre-treatment and post-treatment evaluations. Intra-group comparisons will be performed using repeated-measures analysis of variance (ANOVA or Friedman’s test), followed by either the Student’s t-test or Wilcoxon’s test. Inter-group comparisons will be performed using either one-way ANOVA or the Kruskal-Wallis test. The choice of tests will be determined by the distribution (normal or non-normal) of the data. The level of significance will be set to 5% (*P* <0.05). All comparisons and statistical analyses will be performed using the SPSS program, version 13.0 (Chicago, IL, USA). Cohen’s d will be employed to determine the clinical effect size of the proposed therapies, with the interpretation of the coefficients based on the classification established by Cohen [23]: 0.2 = small effect; ≥0.5 = moderate effect; ≥0.8 = large effect.

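### The 20 to 1000 Hz EMG band at 2 kHz sampling keeps a noise-dominated upper half and leaves no guard band, which can distort low-amplitude resting EMG measures

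*Protocol article*

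**What the plan says.** The Electromyography section fixes two acquisition settings. Signals are collected "using a band-pass filter with a cutoff frequency of 20 to 1000 Hz and common-mode rejection ratio >120", and digitised "with a sampling frequency of 2 kHz". It gives no filter order, roll-off or noise floor.

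For the resting condition, "the volunteer will remain with the mandible relaxed, teeth apart and lips in contact for 15 s". Under Electromyography signal processing, "With the mandible at rest, the RMS will be calculated for the entire 15 s of the signal collected"; this value is then expressed as a percentage of the maximum voluntary contraction (MVC), and mean normalised activity is compared across the evaluation times.

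The same section says: "The root mean square (RMS), median frequency, asymmetry index and co-contraction index will be used as the parameters". It does not say in which condition the median frequency is computed. In the Data analysis section, "EMG will be the secondary outcome".

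**The concern.** Half of 2 kHz is 1000 Hz, so the upper cutoff sits exactly at the highest frequency the sampling can represent. A conventional filter is only about 3 dB down at its cutoff and falls off gradually, so some content above 1000 Hz can fold back into the record. Separately, the wide band keeps everything from 500 to 1000 Hz, where surface EMG has little power but broadband noise has about half of its own.

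Neither matters much when the muscle signal is strong. At rest it is weak, and noise can then form a material share of any amplitude or frequency measure. That share changes whenever EMG amplitude changes. A real fall in resting amplitude is diluted by the constant noise. If median frequency were also computed at rest, the same fall would push it upward with no change in the muscle spectrum, and one effect could be read as two. The hypothesis includes a change in masticatory EMG activity, so the measure should be as clean as is cheaply possible.

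**Working it through.** **Inputs from the article.** Upper cutoff 1000 Hz, lower cutoff 20 Hz, sampling 2 kHz, resting RMS over 15 s.

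**Assumptions, not in the article.** Butterworth low-pass of order 2, 4 or 8; white noise, also above the cutoff (a worst case for folding); EMG spectrum proportional to f²/((f²+fl²)(f²+fh²)²) with (fl, fh) = (60, 120) or (80, 200) Hz. These two spectra have medians of about 97 and 149 Hz, with 96 to 99% of power below 500 Hz. The resting EMG-to-noise amplitude ratio r is 1.5 to 3.

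**Step 1: guard band.** 2000/2 = 1000 Hz; cutoff divided by this limit = 1.00. There is no guard band.

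**Step 2: noise in the upper half.** (1000 − 500)/(1000 − 20) = 500/980 = 51% of flat in-band noise, against 1 to 4% of the modelled EMG power.

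**Step 3: folded noise.** Integrate the power gain 1/(1 + x^(2n)), with x in units of 1000 Hz, above and below x = 1. For order 2 this is 0.244/0.867 = 0.281. Order 4 gives 0.110 and order 8 gives 0.049. Content from 1000 to 1500 Hz folds to 1000 down to 500 Hz; that range holds 62%, 92% and 99.7% of the noise passed above the cutoff at orders 2, 4 and 8.

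**Step 4: resting RMS.** Set in-band noise power to 1 and let v be total noise power. After a true 30% fall (0.7² = 0.49) the observed RMS ratio is √[(0.49r² + v)/(r² + v)].

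- r = 1.5, v = 1.28 (order 2): √[(1.1025 + 1.28)/(2.25 + 1.28)] = √0.675 = 0.822, a fall of 17.8%.
- r = 3, v = 1.05 (order 8): √[(4.41 + 1.05)/(9 + 1.05)] = √0.543 = 0.737, a fall of 26.3%.
- With a 500 Hz low-pass, v is about 480/980 = 0.49. For r = 1.5, √(1.5925/2.74) = 0.762, a fall of 23.8%. For r = 3, √(4.90/9.49) = 0.719, a fall of 28.1%.

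With the filter slope included, the spectrum model gives 18 to 26% as written and 23 to 28% with the low-pass. The lower end becomes 22% if noise already folded below 500 Hz is counted. The MVC denominator has high amplitude and is barely affected, so the dilution carries through to the normalised value.

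**Step 5: median frequency, if taken at rest.** The same 30% fall, with the EMG spectrum unchanged:

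| EMG-to-noise ratio | As written | 500 Hz low-pass |
|---|---|---|
| 1.5 to 3 | +7 to +43% | +2 to +12% (up to 14% counting noise folded below 500 Hz) |
| 5 | 4% or less | smaller |
| 10 | 1% or less | smaller |
| 20 (clenching) | about 0.2% | smaller |

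**Step 6: which source?** With folding switched off, the range at ratios 1.5 to 3 is still +6 to +33%. At order 4 and ratio 2, the shift is +17.3% without folding and +20.2% with it (first spectrum), or +13.6% and +16.0% (second). A perfect 1000 Hz filter with no folding gives +18.0% and +14.4%.

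A separate model with corners at 60 and 200 Hz agrees. When the ratio halves from 2 to 1, the median moves from 162.5 to 240.5 Hz (+78 Hz) at order 4 with folding, from 162 to 237 Hz (+75 Hz) with a perfect filter, and from 141.5 to 161.5 Hz (+20 Hz) with a 500 Hz fourth-order cutoff.

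**The case against.** A reader might infer from the coincidence of cutoff and half the sampling rate that aliasing drives the distortion. The documents and the arithmetic do not support that. Most of the shift is ordinary in-band noise and appears with a perfect filter. In the halving model, folding accounts for about 30%, 17% and 9% of the shift at orders 2, 4 and 8, and dominates only for a first-order filter (about 54%). The article gives neither the filter order nor the noise above 1000 Hz. Aliasing cannot be excluded, but it is not shown.

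A reader might also infer that the trial will report a false rise in median frequency. That requires median frequency to be computed on the resting record. The article lists the parameter but names only RMS for that record, so the consequence is conditional. It also requires a low signal-to-noise ratio, about 3 or less for the larger shifts, and no noise figure is given.

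The signals are processed in Matlab routines that a journal article need not describe in full, so a further digital filter may already exist. The silence is not counted against the plan; the point rests on the two stated settings. The gain for RMS is modest, the same recording chain serves all arms, and the primary outcome, pain by VAS and algometry, is untouched.

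These objections limit the cause, the certainty and the weight of the point. They do not remove it: the resting RMS is an explicitly planned analysis, and the stated band admits noise that it does not need.

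**Conclusion.** The point holds as a minor, conditional one. The stated band keeps a 500 to 1000 Hz region with about half of any broadband noise and 1 to 4% of the modelled EMG power, and it leaves no guard band.

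Under the assumed noise and spectra, with resting EMG at 1.5 to 3 times the noise RMS, a true 30% fall in resting amplitude would be seen as about 18 to 26%; a 500 Hz low-pass would bring this to 23 to 28%. Should median frequency be computed at rest, it would rise falsely by about 7 to 43%, against 2 to 12%. At a ratio of 5 the false shift is 4% or less, and for clenching records it is negligible.

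The wide noise band is the main source and folding the lesser one. Only the secondary EMG outcome is concerned. It is a cheap improvement, not a threat to the trial's main conclusion.

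**What to change.** In the Matlab routines, apply a zero-phase digital low-pass at 500 Hz to every recording before RMS, median frequency and the indices are computed, and state the analysis band as 20 to 500 Hz. State that median frequency is taken from contraction records only. If the routines already do this, one sentence saying so settles the point.

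The filter removes the upper noise band and most of the folded noise, since content from 1000 to 1500 Hz lands between 500 and 1000 Hz. Faster sampling alone, with the same band, is not sufficient: it would address the folding and leave most of the distortion.

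The cost is one line of code, run identically on all files, including those already recorded, with no new recordings or staff. The downside is the loss of about 1 to 4% of true EMG power, equally in all arms. Some dilution of resting amplitude remains even so. The article reports recruitment under way, so the change is best written down before the EMG data are analysed.
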